## Abstract

**Background:**

Bronchopulmonary dysplasia (BPD) is a chronic disease that affects the immature lungs of preterm infants. Infants born before 32 weeks of gestation are at a greater risk of developing BPD due to the need for respiratory support with higher oxygen requirement.

Pulmonary vascular remodelling in early BPD can impose an additional burden on the right ventricle (RV) and RV dysfunction.

This protocol outlines the study design and aims to formulate a prediction model to identify early BPD through the data generated from echo scans analysis.

**Methods:**

The mixed-methods observational cohort feasibility study, which comprises three work-packages (WPs), will be conducted at the regional neonatal unit, University Hospital Plymouth, Plymouth, UK. WP-I will recruit 40 preterm infants; each participant will have two heart scans performed in the first ten days after birth (DABs).

WP-II will collect the documentation of the participating preterm infants’ parents in the study neonatal unit diaries in the first 10 DABs. WP-III will involve semi-structured interviews of 10–15 parents of participating preterm infants and 10–15 health professionals who participated in WP-I.

The study recruitment will be conducted over 18-months. The start date is 01 June 2022. WP-I and WP-II recruitment will occur during this period, while WP-III recruitment will occur during the second half. The results are expected to be submitted for publication by mid-2024.

**Discussion:**

This paper outlines the study design. If the study successfully identifies the most sensitive echo parameter in recognising the RV dysfunction associated with early BPD, it will be an important finding in constructing an early BPD prediction model.

**Trial registration:**

ClinicalTrials.gov Identifier is NCT05235399

## Background

Bronchopulmonary dysplasia (BPD), also known as chronic lung disease, was first identified in 1967 [1]. This condition mainly affects the immature lungs of preterm infants. In the UK, about one third of preterm infants born before 32 weeks of gestation are diagnosed with BPD [2]. Hence, the National Neonatal Audit Programme (NNAP) recommendations urge healthcare professionals to identify potential changes in practices that can improve the respiratory function of preterm infants [2].

BPD negatively affects the normal growth and development of the immature lungs’ alveoli and vascular bed [3]. A recent study, despite its limitation of being an animal study, showed a crucial finding when it demonstrated that changes in the pulmonary capillary bed occur prior to those in the lungs’ parenchyma, which supports the vascular theory; the pathological process of BPD starts in the pulmonary vascular bed [4]. The pulmonary vascular remodelling in BPD affects preterm infants, resulting in a rise in the vascular tone, altered reactivity, vasoconstriction and increased pulmonary vascular resistance [5]. These changes generate a higher right ventricle (RV) afterload pressure. Subsequently, the chronic increase in RV afterload pressure and hypoxic episodes can result in RV dysfunction, hypertrophy and, in severe cases, RV failure [6]. Furthermore, severe forms of BPD are associated with a higher incidence of pulmonary arterial hypertension [7], which is associated with significant co-morbidities and high mortality rates [8].

Additionally, BPD commonly causes adverse effects, such as poor health, longer hospital stays, prolonged need for oxygen therapy, neurodevelopmental delay and a higher rate of death in affected preterm infants [9, 10].

The diagnostic definition of BPD is mainly based on the oxygen requirements and respiratory support at 28 days and 36 weeks of postmenstrual age (PMA) [11–13] without any inclusion of pathophysiological changes of early BPD [14].

The recent classifications of BPD divide the disease into grades I, II, III and/or III(A) according to its severity [12, 13]. These classifications [12, 13] include additional modalities of respiratory support, such as Humidified Heated High Flow Nasal Cannula, which was not included in the previous definition by Jobe and Bancalari [11]. Irrespective of the diagnostic definition used, the formal diagnosis and severity of BPD will not be established until the preterm infant is 36 weeks of PMA or at discharge (if the infant is discharged prior to that).

Czernik et al. [15] demonstrated a persistently elevated myocardial performance index of the RV in the first 2 weeks after birth (WABs) in preterm infants with incipient BPD. The identification of RV dysfunction associated with early BPD through echocardiography (echo) scan examination in these 2 weeks can serve as a marker for detecting preterm infants with the condition [15, 16].

The data obtained from 1735 infants born between 23 and 30 weeks of gestational age showed that the proportion of these infants needing oxygen decreases from birth to the 7th day after birth (DAB). This is followed by a steep rise in the number of infants requiring oxygen in the same cohort at the start of the second WAB [17]. These studies indicated that pathological pulmonary changes start as early as the first WAB [15, 17].

This paper describes the protocol of the proposed clinical study, which examines the applicability of RV functional assessment in an early BPD prediction model. This study protocol details three work packages (WPs): WP-I, which comprises the performance of two echo scans at the 5th and 9th DABs; WP-II, which is an embedded qualitative research project that aims to examine the parental perception of their participating preterm infants’ health; this is performed by analysing the parental written notes in the neonatal unit diary in the first 10 DABs; and WP-III, which is a further qualitative research project that involves conducting semi-structured interviews with 10–15 parents of the participating preterm infants and 10–15 health professionals who are involved in the initial phases of this study.

This study (REPORT-BPD) aims to capture the burden exerted on the RV by early BPD and its associated pulmonary vascular changes by performing functional echo examinations at two time points—5th and 9th DABs—and identifying the most sensitive echo scan parameter to diagnose RV dysfunction. The findings will be used to construct an early BPD prediction model.

The embedded qualitative research components are added to this project as qualitative research methodologies are commonly used by researchers to explore the shortfalls and adjustments required for the planned larger trial [18].Feasibility outcomes and progression criteria1.1.Primary outcome:1.1.1.The feasibility of constructing a prediction model of BPD through diagnosing RV dysfunction associated with early BPD1.2.Secondary outcomes:1.2.1.Identification of the most sensitive echo parameter(s) to diagnose early BPD-associated RV dysfunction1.2.2.Establishing if adjustments are needed to the study procedures, such as screening, recruitment and performance of echo scans, to maximise recruitment and minimise data loss1.2.3.Establishment of recruitment and retention rates for preterm infants with and without BPD, i.e. cases and controls1.2.4.Obtaining descriptive statistical data about the study cohort and the selected echo parameter(s) will facilitate the estimation of the sample size needed for the definitive large study1.3.Progression criteria:The following progression criteria should be met1.3.1.Constructing a BPD prediction model based on a sensitive echo parameter in detecting early BPD-associated RV dysfunction is a key criterion to progress to a definitive large study1.3.2.Satisfactory recruitment and retention rate of preterm infants with and without BPD1.3.3.Logistical challenges in performing the echo scans; two should have been performed on most of the recruited preterm infants (≥ 80)1.3.4.Most of the echo scans (≥ 80%), especially the Tissue Doppler Imaging (TDI) and the speckle tracking clips and images, should be suitable for analysis by the cardiology analysis system (TomTec, Germany)

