**WP-I and WP-II**									
**Procedures**	**Antenatally**	**1st DoPL©**	**2nd DoPL©**	**Data collection**					
				**T0**	**T1**	**T2**	**T3**	**T4**	**T5**
Screening and eligibility assessment	**√**^a^	**√**	-	-	-	-	-	-	-
Initial conversation with the research team	**√**^a^	-	**√**	-	-	-	-	-	-
Informed consent	-	-	**√**	-	-	-	-	-	-
Demographics (when consent obtained)	-	-	**√**	-	-	-	-	-	-
Echo scan on 5th DoPL	-	-	-	**√**	-	-	-	-	-
Echo scan on 9th DoPL	-	-	-		**√**	-	-	-	-
Working weight	-	-	-	**√**	**√**	-	-	-	-
Vital signs including systolic, diastolic, and mean Blood Pressure (BP)	-	-	-	**√**	**√**	-	-	-	-
Collection of NICU parents/patients’ diary copies	-	-	-	-	-	**√**	-	-	-
Collection of data related to outcomes/diagnosis of BPD	-	-	-	-	-	-	-	**√**	-

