#### Data collection and analysis

Echo scans and clinical and demographic data will be collected.

Demographic data, including birth gestation in weeks, birth weight, sex, Apgars, chorioamnionitis, maternal hypertension, antenatal steroids, and magnesium sulphate, will be collected.

Functional neonatal echo scans will be performed, collected and stored on the 5th and 9th DABs of the recruited preterm infants. They will be collected as per the developed echo image acquisition guide, which is in compliance with the expert consensus statement produced by the American Society of Echocardiography in collaboration with the European Association of Echocardiography and the Association for European Pediatric Cardiologists [21]. Numerous echo parameters, such as global and segmental strain and strain rate for right and left ventricles (RV and LV), tissue Doppler imaging (TDI) of RV free wall, septal and LV lateral wall to measure the S, E’ and A’ waves together with isovolumic contraction and relaxation times, will be collected. Other echo parameters related to pulmonary arterial pressure, cardiac function and ductus arteriosus (DA) assessments such as tricuspid regurgitant jet, pulmonic valve insufficiency, pulmonary artery acceleration time (PAAT), right ventricle ejection time, tricuspid annular plane systolic excursion (TAPSE), mitral annular plane systolic excursion (MAPSE), shortening fraction of the LV and DA size and shunt assessment, will be collected too. Also, right ventricular systolic pressure and myocardial performance indices of RV and LV, will be calculated.

These scans will be analysed using a specialised cardiology analytic system (TomTec, Germany).

In addition, clinical data, vital signs, current weight and ventilatory support will be collected.

The distribution of all continuous variables will be visualised to check for normality and summarised using appropriate descriptive statistics. Preterm infants will be categorised into two groups: (i) moderate or severe BPD and (ii) mild or no BPD.

Velocities and displacements are dependent on cardiac size. Therefore, it is crucial to normalise the measurements taken for cardiac size [22]. The left ventricle septal length will be used to normalise all echo measurements of interest.

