**Work package—I**	• Establishing sensitive and feasible echo parameters for detecting right ventricle dysfunction associated with early BPD pulmonary vascular changes • Suitability of eligibility criteria and sample characteristics • Fidelity to the study procedures such as recruitment, data collection including echo scan performance at the set time points • Recruitment, accrual, and retention rates
**Work package—II**	• To gain an understanding of how strong the correlation between the parents’ views of their infant’s health development during the first 10 days of postnatal life and the findings of echo scans at the same period
**Work package—III**	• To gain an understanding of parents and healthcare professionals in participating in the study and identify barriers and enabling factors to inform the methods a full trial

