## Discussion

The current scientific literature shows that early BPD starts in the first WAB of the affected preterm infants, with the respiratory function decline manifesting at the 7th day of postnatal life [17]. In addition, animal research findings support the vascular theory, indicating that the vascular changes in early BPD start before the pulmonary parenchymal ones [4]. These findings form the foundation for structuring the proposed study. The research team will perform two echo scans two days before and after the 7th DAB. This will allow a closer examination of RV functional changes in preterm infants with early BPD compared to healthy ones.

The strengths of this study can be summarised as follows. First, it uses two echo scans around the timepoint of change in the pulmonary function. Second, it uses only non-invasive intervention (echo scans). Our tertiary NICU is well-positioned to conduct the study since our experienced neonatal team regularly performs haemodynamic assessments with functional neonatal echo scans. Third, a combination of advanced technologies will be used to assess the RV function (e.g. TDI and speckle tracking). The proposed study will not only highlight the most sensitive echo parameters through the study analysis but also help in identifying if one echo scan, either day 5 or 7 of postnatal life, is adequate to diagnose the early BPD-associated RV dysfunction.

The functional echocardiographic examinations of ductus arteriosus and pulmonary arterial pressure will allow the study team to investigate its effect on the echo parameters related to the RV function in preterm infants with BPD and controls.

The main limitation of the study is that it is an observational study since a randomised controlled trial is not an appropriate design to answer our research question.

To the best of our knowledge, this is the first study performing two echo assessments at 5th and 9th DABs using a combination of the most recent cardiac technologies to analyse the acquired neonatal echo scans. The study findings will allow the formulation of an early BPD predictive model. The future plan is to test this model in a large multi-centre trial.

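### The study can show which day 5 and day 9 echo parameters discriminate later BPD, but not which is most sensitive for RV dysfunction, because RV dysfunction is never established independently of those parameters

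*Protocol article*

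**What the plan says.** The target condition is RV dysfunction in several places of the protocol article:

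- The aim, in the Background, is stated as "identifying the most sensitive echo scan parameter to diagnose RV dysfunction".
- Secondary outcome 1.2.1 reads "Identification of the most sensitive echo parameter(s) to diagnose early BPD-associated RV dysfunction".
- Progression criterion 1.3.1 begins "Constructing a BPD prediction model based on a sensitive echo parameter in detecting early BPD-associated RV dysfunction is a key criterion".
- Table 3 gives as a WP-I outcome measure "Establishing sensitive and feasible echo parameters for detecting right ventricle dysfunction associated with early BPD pulmonary vascular changes".
- The WP-1 section on data collection and analysis says that finding the parameters most sensitive for RV dysfunction will help to construct the BPD model.

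The same WP-1 section sets out what is observed and compared. The RV measures are all echo measures: strain and strain rate, tissue Doppler, TAPSE, pulmonary artery acceleration time, tricuspid regurgitant jet and others. In addition, "right ventricular systolic pressure and myocardial performance indices of RV and LV, will be calculated". The grouping is: "Preterm infants will be categorised into two groups: (i) moderate or severe BPD and (ii) mild or no BPD". Parameters are compared between these groups with t-tests, Mann–Whitney U tests and chi-squared tests.

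In Table 1 the only later outcome is "Collection of data related to outcomes/diagnosis of BPD", at T4, which is 36 weeks PMA or earlier discharge. No other cardiac assessment is listed.

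The Discussion describes the contrast as "RV functional changes in preterm infants with early BPD compared to healthy ones".

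**The concern.** Sensitivity is the proportion of those with a condition whom a test detects. To rank echo parameters by their sensitivity for RV dysfunction, some infants must be known to have RV dysfunction by a means other than the parameters being ranked. The article describes no such means. What it provides is a comparison of echo values between infants who later do and do not meet a respiratory definition of BPD.

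Two statements are at stake. The study could report a parameter as the most sensitive for RV dysfunction when it had only shown an association with BPD some weeks later. The qualifier in 1.3.1, a criterion described as key to progression, could be recorded as met on a property that was not measured.

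The description of the controls adds to this. A reader of the Discussion would expect healthy infants, but the control group includes mild BPD, and under Table 2 every infant enters because an echo scan is clinically indicated.

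**Working it through.** The plan has no figure to reproduce on this point. The target of 40 infants is set as realistic for recruitment, not from a power calculation. The check is therefore mainly a comparison of what is promised with what is observed.

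**1. Is there a reference for RV dysfunction?** The data listed for WP-I are demographics, clinical data, vital signs, weight, ventilatory support, the two echo scans and BPD status. Each RV measure is a candidate parameter or is derived from the same scans. Choosing one of them as the reference, for example the RV myocardial performance index, would be circular: that index would be fully sensitive by construction, and the others would be judged on agreement with it.

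**2. Can BPD status stand in for RV dysfunction?** The Background says that BPD is defined mainly by oxygen need and respiratory support and that the definition includes no pathophysiological change. It also presents RV dysfunction as something that raised afterload can cause, not as something always present. So BPD without RV dysfunction is possible, and so is the reverse.

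**3. What happens if BPD is used as the reference anyway?** Let q be the share of infants with moderate or severe BPD who have RV dysfunction at the scan. Let Se and Sp be a parameter's sensitivity and specificity for RV dysfunction, assumed to be the same whatever the later BPD status. Then:

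sensitivity against BPD = q × Se + (1 − q) × (1 − Sp)

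With Se = Sp = 0.90 (assumed; no such value is in the article):

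| q (assumed) | Calculation | Sensitivity against BPD |
|---|---|---|
| 0.30 | 0.30 × 0.90 + 0.70 × 0.10 | 0.34 |
| 0.50 | 0.50 × 0.90 + 0.50 × 0.10 | 0.50 |
| 0.70 | 0.70 × 0.90 + 0.30 × 0.10 | 0.66 |
| 0.90 | 0.90 × 0.90 + 0.10 × 0.10 | 0.82 |
| 1.00 | 1.00 × 0.90 + 0.00 × 0.10 | 0.90 |

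The same holds in the controls. If a share f of them has RV dysfunction, specificity against BPD = 1 − [f × Se + (1 − f) × (1 − Sp)]. For f = 0, 0.10 and 0.30 this gives 0.90, 0.82 and 0.66.

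Neither q nor f is observed, so Se cannot be recovered from the comparison by BPD status. A larger sample would not change that: about 13 of 40 infants are expected in the BPD group (40 × 1/3, the fraction given from the 2018 admissions), but the number with RV dysfunction among them is undefined at any sample size.

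**4. What remains answerable?** BPD status and the echo values are both collected, so the discrimination of moderate or severe from mild or no BPD by each day 5 and day 9 parameter can be estimated. A BPD model with gestational age, oxygen requirement and ventilatory support can also be built.

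**The case against.** The strongest reply is that the wording is loose but the meaning is clear. The target is RV dysfunction associated with early BPD, not RV dysfunction in general. The WP-1 objective says that the parameters are for inclusion in a model to identify early BPD, the analysis compares BPD groups, and no sensitivity proportion for RV dysfunction is planned. On this reading, sensitive means responsive to BPD-related RV change, and the design serves prediction. That is a fair account of what the study will do. It does not rescue the stated outcome, because the text describes two steps, first a parameter sensitive for RV dysfunction and then a BPD model based on it, and only a direct comparison by BPD status is available. If the looser meaning is intended, the wording should say so.

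It can also be said that the article is condensed, and that the image acquisition guide and Fig. 1 are not shown. A cut-off for an echo index may well stand in the full documents, and its absence here is no fault. A separate reference assessment, however, would be expected in the procedures of Table 1, and a cut-off on a candidate parameter would not supply one.

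Three stronger readings are tempting, and the documents do not support them:

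- A reader might infer that criterion 1.3.1 as a whole, or primary outcome 1.1.1, cannot be met. BPD status is observed at T4, so the model can be built and judged against it. Only the RV-dysfunction qualifier fails.
- A reader might infer that the influence of the ductus on RV measures has been overlooked. The Discussion already plans to examine the effect of the ductus and of pulmonary arterial pressure on the RV parameters in both groups, and the model includes oxygen and ventilatory support.
- A reader might take the table of apparent sensitivities as an estimate of bias. Its inputs are assumed, and it shows only that the quantity is not identified.

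**Conclusion.** The point stands in a limited form. The aim, outcome 1.2.1, the qualifier in 1.3.1, the WP-1 analysis text and Table 3 promise sensitivity for early BPD-associated RV dysfunction. The design as described can deliver discrimination of later BPD, but not that. Building and judging a BPD model is not affected.

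The size cannot be given as a number from the documents. The consequence is for what may be concluded: a ranking of parameters by sensitivity for RV dysfunction, and a progression statement that relies on it, would have no reference behind them. This rests on Table 1 and the WP-1 data list being complete as to cardiac assessments. Describing the controls as healthy is a smaller inaccuracy in the Discussion, since the analysis section defines the group clearly.

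**What to change.** Restate the aim, outcome 1.2.1, the qualifier in criterion 1.3.1, the analysis text of WP-1 and the WP-I row of Table 3 in terms of what is observed: the day 5 and day 9 echo parameters that best discriminate moderate or severe BPD from mild or no BPD at 36 weeks PMA or earlier discharge. Present RV dysfunction as the proposed mechanism rather than the condition diagnosed. In the Discussion, replace the reference to healthy infants with the actual control group, those with mild or no BPD.

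No change to recruitment, scans, data collection or sample size is needed. The cost is that the stated claim becomes more modest. A breakdown by ductal status is largely covered by what the Discussion already plans and is not part of this fix.

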## Methods

The study procedures and flow for all three WPs, from screening to data analysis, are summarised in Fig. 1 and Table 1.

**Fig. 1 Fig1:**
[figure not shown]
Study flow charts for all work packages

**Table 1 Tab1:** Study procedures for all work packages

**WP-I and WP-II**									
**Procedures**	**Antenatally**	**1st DoPL©**	**2nd DoPL©**	**Data collection**					
				**T0**	**T1**	**T2**	**T3**	**T4**	**T5**
Screening and eligibility assessment	**√**^a^	**√**	-	-	-	-	-	-	-
Initial conversation with the research team	**√**^a^	-	**√**	-	-	-	-	-	-
Informed consent	-	-	**√**	-	-	-	-	-	-
Demographics (when consent obtained)	-	-	**√**	-	-	-	-	-	-
Echo scan on 5th DoPL	-	-	-	**√**	-	-	-	-	-
Echo scan on 9th DoPL	-	-	-		**√**	-	-	-	-
Working weight	-	-	-	**√**	**√**	-	-	-	-
Vital signs including systolic, diastolic, and mean Blood Pressure (BP)	-	-	-	**√**	**√**	-	-	-	-
Collection of NICU parents/patients’ diary copies	-	-	-	-	-	**√**	-	-	-
Collection of data related to outcomes/diagnosis of BPD	-	-	-	-	-	-	-	**√**	-
